### Participants

At least 152 community-dwelling men and women aged 65 years and over will be invited to participate in this study.

#### Recruitment

The intervention will be implemented across a number of local community-based health and fitness centres within Melbourne and surrounding areas in Victoria, Australia. Recruitment and testing of participants will be staggered and split into two cohorts over 2-years, each starting at the same time of the year, to facilitate the management and implementation of the trial. A variety of recruitment strategies will be employed to attract participants, including information talks at community centres, local media campaigns including newspaper and magazine advertisements, flyers placed on relevant notice boards and word of mouth. All participants that express an interest in being involved in the study will undergo screening to determine their eligibility to participate in the trial based on the criteria outlined below.

#### Screening and eligibility

Screening will consist of a four-step process. First, all participants will be screened over the telephone and deemed ineligible based on the following criteria: 1) aged <65 years; 2) current or prior participation in resistance exercise (>1 day per week) and/or moderate-intensity physical activity ≥150 minutes per week in the past 3 months; 3) acute or terminal illness, including current (treated or untreated) cancer or surgery/cessation of chemotherapy/radiotherapy less than 12-months ago; 4) history of a recent low trauma fracture with functional impairment that would limit participation in the exercise program; 5) body mass index (BMI) >40; 6) use of insulin to treat diabetes; 7) chronic liver disease, coeliac or inflammatory bowel disease, including ulcerative colitis or Crohn’s disease; 8) recent use of oral corticosteroids (past 6 months); or 9) inability to commit to the study and its requirements. Participants will not be excluded if they are currently taking vitamin D supplements, but will be asked to take the vitamin D that is provided to them as part of the study so that we are able to monitor compliance. Second, eligible participants will then be asked to complete the Short Portable Mental Status Questionnaire (SPMSQ) and the Geriatric Depression Scale (GDS) to evaluate whether they are cognitively healthy and have no signs of depression. Those with a score of greater than two on the SPMSQ and/or a score of greater than six on the GDS will be excluded from the study. For these participants, a letter will be sent to their doctor and they will be encouraged to make an appointment with them to discuss this is in further detail. Participants that remain eligible will then be required to obtain approval from their local doctor to clear them of any contraindicated medical conditions to exercise, based upon American College of Sports Medicine (ACSM) guidelines, to participate in the program. Finally, participants will be asked to provide a fasted, morning blood sample to confirm that their estimated Glomerular Filtration Rate (eGFR) is >45 mL/min/1.73m^2^. Written informed consent will be obtained from all participants prior to commencing the program.

#### Randomisation and blinding

Randomisation will be at the level of the individual participant in blocks of four, stratified by gender, using a computer-generated random number sequence by an independent researcher. Neither the participants nor research staff involved in the testing will be blinded to the allocation, but those analysing the data will be blinded. A flow diagram of the study protocol is outlined in Fig. 1.

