## Methods

### Study design

This is a 48-week randomised controlled trial consisting of a 24-week intervention with a 24-week follow-up. Men and women aged 65 years and over will be randomly allocated to one of two groups: 1) PRT with two 80g servings of cooked lean red meat on each of the three days that they complete their exercise session (RT+Meat group), or 2) control PRT in which participants will be provided with and advised to consume ≥1 serving (~1/2 cup) of rice and/or pasta or 1 medium potato on each of the three training days [control resistance training (CRT)]. On the non-training days, the red meat group will be instructed to maintain their usual diet whilst those in the CRT group will be asked to continue to incorporate larger servings of breads, cereals, rice, pasta and vegetables (carbohydrates) and smaller amounts of protein foods (e.g. meat, fish and chicken). All participants will be asked to take a daily vitamin D supplement (1000 IU) and encouraged to maintain a healthy diet that includes the recommended amounts of fruits and vegetables and dietary calcium throughout the entire study. At the completion of the 24-week intervention, all participants will be encouraged to continue to undertake the exercise program (at their own expense) and those in the red meat group were provided with dietary advice to maintain a protein rich diet (at least 1.2 g/kg/day) including red meat which will be monitored at weeks 36 and 48. The trial is managed by the Centre for Physical Activity and Nutrition Research at Deakin University, Burwood, Melbourne, Australia and is funded by a nationally competitive grant from Meat and Livestock Australia. The study has been approved by the Deakin University Human Research Ethics Committee (HREC 2013–166), and is registered with the Australian and New Zealand Clinical Trials Registry (ACTRN12613001153707).

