## Trial status

Recruitment is currently underway and a number of participants have commenced the study.

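### A single published block size of four within sex, with unblinded testing staff, leaves up to one third of allocations foreseeable; randomly varied, undisclosed block sizes would be a cheap improvement

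*Protocol article*

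**What the plan says.** Under Randomisation and blinding, the protocol article fixes the scheme: "Randomisation will be at the level of the individual participant in blocks of four, stratified by gender". The list is produced "using a computer-generated random number sequence by an independent researcher". The same section says: "Neither the participants nor research staff involved in the testing will be blinded to the allocation". Only those analysing the data are blinded.

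Under Study design, participants "will be randomly allocated to one of two groups". The 1:1 ratio is implied but not written out. Under Recruitment: "Recruitment and testing of participants will be staggered and split into two cohorts over 2-years". Under Outcome measures, baseline and week 24 testing take place at one university centre. Under Trial status: "Recruitment is currently underway and a number of participants have commenced the study".

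The article mentions only one block size and does not say that it is withheld from recruiting or testing staff. It also does not say whether participants are randomised one at a time or in batches.

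**The concern.** A small, constant block size protects allocation only while nobody near enrolment can reconstruct the sequence. Three stated features make reconstruction easier here. The block size is four and has been published, there are only two running sequences to follow (men and women), and the staff who test participants know the allocations. Having an independent person generate the list protects the list itself, but it does not stop someone who has seen the earlier part of a block from working out its end.

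If a person who can influence entry or baseline testing foresees the next arm, the groups can come to differ in ways that no baseline variable captures. Most eligibility criteria are thresholds or external clearances, but some involve judgement, such as whether a volunteer can commit to the study (Screening and eligibility). One primary outcome, the 3-RM leg press, depends on effort and on the tester's judgement of technique and choice of warm-up load (Muscle strength), so a baseline value could also be affected. Blinding the analysts comes too late to help, and the planned adjustment for baseline imbalance cannot correct for unmeasured selection.

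**Working it through.** The article gives no predictability figure, so there is none to reproduce.

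**Inputs**
- Block size 4, strata men and women: Randomisation and blinding.
- Two arms: Study design. Two of each arm per block (1:1) is assumed.
- 152 participants in total: Abstract and Participants. The Sample size calculations section words 152 as a per-group number. The shares below do not depend on which is right; the count would scale with the total.
- The sex split is not given, so a range is shown.

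**Step 1: allocations that are certain.** There are C(4,2) = 6 equally likely blocks: AABB, ABAB, ABBA, BAAB, BABA, BBAA. An allocation is certain once one arm is used up in the block.
- Positions 1 and 2: never certain.
- Position 3: certain in AABB and BBAA, so 2/6 = 1/3.
- Position 4: always certain.

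Share = (0 + 0 + 1/3 + 1)/4 = (4/3)/4 = **1/3** (8 of the 24 positions across the six blocks).

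**Step 2: best guess.** The best guess is the arm with more places left.
- Position 1: 1/2.
- Position 2: 2/3.
- Position 3: (1/3 × 1) + (2/3 × 1/2) = 2/3.
- Position 4: 1.

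Success = (1/2 + 2/3 + 2/3 + 1)/4 = 17/24 = **70.8%**, against 50% with no information.

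**Step 3: scaling to 152.** Each complete block contributes 4/3 expected certain allocations. An incomplete last block contributes 0, 0 or 1/3 after one, two or three places.
- 76/76: 38 complete blocks × 4/3 = 50.7 (33.3%).
- 61/91: (15 × 4/3) + (22 × 4/3 + 1/3) = 20 + 29.7 = 49.7 (32.7%).
- 46/106: (11 × 4/3) + (26 × 4/3) = 14.7 + 34.7 = 49.3 (32.5%).

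These are expected counts for an observer who knows the block size and every earlier assignment in the stratum before the next person is enrolled. If a whole cohort is randomised together after baseline, nothing is foreseeable at enrolment or baseline. The range is therefore **0 to about 50**.

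**Step 4: what varied blocks would change.** Fixed sizes were enumerated as above. Mixed sizes were evaluated in 3,000 simulated strata of 76, with an observer who knows the set of sizes but not their order and updates the probabilities after each assignment.

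| Scheme | Certain | Best guess correct |
|---|---|---|
| Fixed 4 | 33.3% | 70.8% |
| Fixed 6 | 25.0% | 68.3% (41/60) |
| Fixed 8 | 20.0% | 66.6% (373/560) |
| Random 4 and 6 | 5.5% | 69.1% |
| Random 4, 6 and 8 | 2.2% | 67.9% |

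Varying the size nearly removes certainty but lowers best-guess accuracy by only about 2 to 3 percentage points.

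**Step 5: balance.** The largest possible imbalance within a sex stratum is half the block size: 4/2 = 2 with blocks of four, and 8/2 = 4 if blocks of eight are included.

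**The case against.** The strongest reply is that the enumeration is correct but the conditions that make it matter are not in the article. The unblinded staff are those involved in testing. The article does not say that they recruit, screen or decide entry, or that they see a running record of assignments. Two cohorts, each starting at the same time of year, are compatible with batch randomisation after baseline. Centre is not a stratification factor, so staff at one fitness centre would see only part of a stratum. Concealment and the timing of release are details that an article commonly leaves to the full protocol, and the flow diagram is not reproduced in the text at hand. Most eligibility criteria leave little room to steer entry.

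Much of this stands. It makes one third an upper bound and rules out treating the absence of a concealment procedure as a fault. It also blocks some stronger readings. A reader might infer that about 50 allocations were in fact known, or that selection bias has occurred; nothing in the article shows either. A reader might infer that the rest of a block can always be deduced, but after one assignment, or after one of each arm, it cannot, and two thirds of allocations are never certain. A reader might infer that allocations are released before baseline testing; the article does not say so.

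What does not fall is the stated choice itself: one small block size, disclosed during recruitment, alongside testing staff who know the allocations and who, at the single university centre, could see whole strata. A less predictable scheme costs almost nothing.

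**Conclusion.** The point holds as a cheap improvement to a stated design choice. It does not identify an invalid method. Under 1:1 allocation and one-at-a-time randomisation, and with someone involved in enrolment or baseline testing who knows all earlier assignments in a stratum, up to one third of allocations are certain in advance and the best guess is right 70.8% of the time. If any of the last two conditions fails, the exposure shrinks, and with batch randomisation after baseline it disappears. The direction and size of any effect on the outcomes cannot be derived from the article. The benefit of a change also depends on how many participants remain to be randomised, which the article does not state.

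**What to change.** For everyone still to be randomised, including any remaining cohort, the independent researcher should generate a new list with randomly varied block sizes within sex, for example 4, 6 and 8, and should not disclose the sizes to recruiting or testing staff. The point at which the list changes should be recorded.

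Because varied sizes reduce certainty much more than they reduce guessing, the sponsor should also confirm that each allocation is released only after eligibility and baseline testing are complete. If that is already the practice, or if cohorts are randomised in a batch after baseline, one sentence saying so would answer most of the concern.

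The cost is one regenerated list and a possible imbalance within a sex stratum of up to 4 instead of 2. No extra participants, assessments or changes to the interventions are needed.

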### Intervention

#### Exercise program

All participants involved in the study will be prescribed an individually tailored and supervised aerobic, PRT and challenging balance and mobility program. All training will be conducted at local community health and fitness centres and participants will be asked to train on three non-consecutive days per week for 24 weeks. Each training session will last approximately 60–75 minutes, and include: a warm-up and cool-down, 15–20 minutes of moderate intensity [5 to 8 (‘somewhat hard’ to ‘hard’) on the 10 point Borg Rating of Perceived Exertion (RPE) scale] aerobic training (e.g. cycling, treadmill walking, stepping), at least two challenging balance/mobility and postural exercises, and 30–40 minutes of moderate to high intensity PRT. All exercise sessions will be supervised by qualified exercise trainers and will be conducted in small groups where possible (approximately 6–8 per group), but each participant’s program will be individualised. For the first two weeks, participants will be asked to complete three sets of 12–15 repetitions for each resistance exercise using relatively moderate resistance to familiarize themselves with the equipment (free and machine weights), the training protocol, and the correct execution of the exercises. Thereafter, participants will be asked to complete three sets of 8–12 repetitions for at least eight different upper and lower body exercises at an intensity corresponding to 5 to 8 (‘somewhat hard’ to ‘hard’) on the 10 point Borg RPE scale. Some examples of the exercises that will be used throughout the program include: squats, lunges, box step-ups, leg extensions, standing leg curls, hip abductions, calf raises, shoulder press, upright row, bicep curls, wall push-ups, and triceps kickbacks/pushdowns. Where possible, all exercise sessions will be conducted prior to lunch or dinner so that the participants can consume their prescribed meal type as soon as possible following the training. If this is not possible, participants will be instructed to consume one serve of red meat before training or both serves after a training session.

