### Outcome measures

A summary of the primary and secondary outcomes and other relevant covariates is shown in Table 1. All participants will be asked to attend Deakin University at baseline and week 24 to undertake testing, with an intermediary assessment of cognitive function conducted on-site at each health and fitness centre at week 12. With the exception of the fasted blood samples which will be collected at local pathology clinics, and the intermediary assessment, all other outcome measures will be assessed within the Centre for Physical Activity and Nutrition Research within the School of Exercise and Nutrition Sciences at Deakin University, Burwood, Melbourne, Australia.

**Table 1 Tab1:** Summary of the outcome measures

Variables	Data collection method	Data collection points (weeks)				
Primary outcome measures	Baseline	Baseline	12	24	36	48
Muscle mass and cross-sectional area	Dual energy X-ray absorptiometry (DXA) total body and regional lean mass	x		x		
	Peripheral quantitative computed tomography (pQCT) scan at 25% femur site	x		x		
Muscle strength	Leg press	x		x		
	Isometric knee extensor strength	x		x		
Cognitive function	Cogstate Brief Battery computerized tests	x	x	x		
	Behaviour Rating of Inventory of Executive Function-Adult Version (BRIEF-A)	x		x		
Secondary Outcome Measures						
Muscle Function	Four-square step test	x		x		
	4 meter walk	x		x		
	30-second sit-to-stand test	x		x		
	Timed up and go test	x		x		
Fat mass and inter-/intra-muscular fat	DXA (total body and regional) and pQCT (25% femur site)	x		x		
Biochemistry and hormonal measures	Overnight fasted blood collection	x	x	x		
Neurotrophic markers	Overnight fasted blood collection	x	x	x		
Adipokines and Inflammatory markers	Overnight fasted blood collection	x	x	x		
Blood lipids	Overnight fasted blood collection	x	x	x		
Bone mineral density	DXA total body, hip and spine scan	x		x		
Blood pressure	Automated measurement	x		x		
Health related Quality of Life	Short form (SF)-36 version 2 questionnaire	x		x		
Neural plasticity and voluntary activation	Transcranial Magnetic Stimulation (TMS) *	x	x	x		
Additional Measures						
Anthropometry	Height, weight and body mass index (BMI)	x		x		
Health and Lifestyle information	Lifestyle Questionnaire	x		x		
Habitual physical activity	Community Healthy Activities Model Program for Seniors questionnaire	x		x	x	x
Memory and mood	Memory Assessment Questionnaire (MAC-Q)	x		x		

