#### Primary outcome measures

The primary outcome measures will be changes in total body and regional (leg) lean tissue mass and muscle cross-sectional area, muscle strength and cognitive function.

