##### Muscle strength

Lower limb muscle strength will be measured from the leg press machine using a three-repetition maximum strength (3-RM) protocol. The 3-RM is the heaviest weight that an individual can complete three repetitions of an exercise whilst maintaining correct form and technique, which corresponds to ~85 % of an individual’s one repetition maximum strength (1-RM). Prior to the assessment of each individual’s 3-RM leg press strength, they will be required to complete a 5-minute warm-up on an exercise bike. To determine 3-RM, each participant will perform a warm-up set of 8-10 repetitions with a light to moderate load. After the successful completion of a further 6–8 repetitions at a heavier weight selected by the instructing researcher and following a brief rest (~1–2 minutes), the weight will be increased incrementally until only three repetitions with correct technique can be completed. To calculate 1-RM strength, the formula developed by Wathen et al. [51] will be used. In addition to the leg press, isometric knee extensor strength will be measured on the participants’ dominant leg using Lord's strap assembly incorporating a strain gauge (Neuroscience Research Australia, Sydney, Australia). Participants will have one practice trial followed by two maximal tests with a 60 second rest between each test. This test has been shown to have excellent test-retest reliability (Pearson r=0.92) [52]. For analysis, knee extension strength (kg) will be expressed per unit of lower leg length to compensate for the length of the lever arm.

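### Testers are told the diet arm for a primary strength test that rests partly on their own judgement, although the test does not require them to know it

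*Protocol article*

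**What the plan says.** The section on randomisation and blinding settles the matter in one sentence: "Neither the participants nor research staff involved in the testing will be blinded to the allocation". The rest of that sentence limits blinding to the data analysts.

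The primary outcome section lists changes in lean tissue mass together with "muscle cross-sectional area, muscle strength and cognitive function". Table 1 names two strength measures, leg press and isometric knee extensor strength, each taken at baseline and week 24.

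The muscle strength section describes the leg press. After a light to moderate warm-up set, the participant does a further set "at a heavier weight selected by the instructing researcher". Then "the weight will be increased incrementally until only three repetitions with correct technique can be completed". The section does not give the size of the load steps or the criteria for correct technique. Knee extension is read from a strain gauge: "Participants will have one practice trial followed by two maximal tests with a 60 second rest between each test".

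On who does what, the exercise programme section says "All exercise sessions will be supervised by qualified exercise trainers", at community health and fitness centres. Strength is tested elsewhere: "All participants will be asked to attend Deakin University at baseline and week 24 to undertake testing". A local butcher delivers the meat. Research staff check the diet diaries, make the monthly calls about medication and collect the exercise cards. The article does not say whether these are the people who run the strength tests.

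**The concern.** In a 3-RM test the recorded value depends partly on the tester, who decides how heavy the next load is and whether the third repetition counted. As a maximal effort, the test is also open to encouragement, on which the article is silent. A tester who knows the arm, in a trial whose hypothesis favours the meat group, can move the week-24 value in that direction without intending to. Blinded analysts receive that value as data and cannot detect or remove the shift.

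At stake is the false-positive rate for a primary outcome, and for one of the outcomes on which the trial is sized. A larger sample does not help, because a fixed bias becomes easier to declare significant as the standard error shrinks.

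The exposure looks at least partly avoidable. Neither the exercise programme nor the strength test differs by arm, and the article gives no reason why the tester should know the diet.

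**Working it through.** **Where the tester can act**

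- Leg press: load selection, load steps and the technique decision are in the tester's hands. The warm-up, repetition ranges, rest and the definition of 3-RM are already written down.
- Knee extension: the strain gauge gives the reading, and the number of trials and the rest are fixed. Only effort, and any encouragement of it, is open.
- pQCT and DXA: the body composition section fixes the pQCT scan site, slice thickness, voxel size, thresholds, and contour and peel modes, and names the DXA software version. These measures are much less exposed.

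The concern therefore rests mainly on the leg press.

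**The plan's own figure**

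Inputs from the sample size section: difference 18%, SD 30%, two-sided alpha 0.05, drop-out 20%. That section attaches 152 to each group, whereas the abstract and the participants section give 152 as the total. Taking 152 in total:

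- Per arm: 152 / 2 = 76. After drop-out: 76 × 0.8 = 60.8, taken as 61.
- SE = 30 × √(2/61) = 5.43 percentage points.
- Power for 18%: 18 / 5.43 = 3.31, which gives 90.8% by the noncentral t (91.2% by the normal approximation).

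The stated power above 80% is reproduced. Reading 152 as per arm only raises it.

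**False-positive rate under an assumed bias**

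Let the true diet effect be zero and let testing add b percentage points in favour of meat. The test statistic then has noncentrality b / SE on 2n − 2 degrees of freedom, and the rejection probability is P(|T| > t₀.₉₇₅). The article gives no value for b, so b is an assumption.

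| Completers per arm | SE | b = 3 (0.1 SD) | b = 6 (0.2 SD) |
|---|---|---|---|
| 61 | 5.43 | 3 / 5.43 = 0.55; 8.5% | 6 / 5.43 = 1.10; 19.5% |
| 76 (no drop-out) | 4.87 | 3 / 4.87 = 0.62; 9.4% | 6 / 4.87 = 1.23; 23.2% |

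As a check, the normal approximation Φ(b/SE − 1.96) + Φ(−b/SE − 1.96), at 60.8 per arm, gives 8.5% and 19.7%. With it, smaller and intermediate biases of 2 and 5 points give 6.6% and 15.1%. For scale, 6 points is 6 / 18, one third of the difference the trial is designed to detect.

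The rate rises with n for the same b. Masking or scripting the test does not enter the sample size formula, so N and planned power stay as they are.

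**The case against.** The strongest reply is that this is an openly declared limitation, not an error, and that masking may not be practical. Research staff handle diet diaries, monthly calls and exercise cards, and if the same few people also test, no one may be free of diet contact. This stands. A reader might infer from the separation of trainers, butcher and university testing that existing staff could be masked at no cost. The article does not support that reading. It gives no staff numbers and does not say who tests. Separating training from testing also says little here, because the arms differ in diet and not in training.

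Second, load increments and encouragement scripts are details that a journal article commonly leaves to a testing manual. This too stands: their absence from the article is not the fault. The point rests on the choice the article does fix, that testers know the arm. The script is proposed as a safeguard and may already exist.

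Third, a reader might extend the concern to DXA and pQCT. The article does not support that at equal weight, since the pQCT settings are fixed, and the blinding of those analysing the data might already cover scan analysis. Coded scan IDs are a cheap extra.

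Fourth, participants know their own diet and supply the effort, so masking testers leaves that route open. This is correct and limits the gain, most clearly for knee extension. It does not touch the tester's own contribution to the leg press.

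Finally, the false-positive figures could be read as an estimate of the bias in this trial. They are not.

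**Conclusion.** The concern holds in a limited form. By its own statement the plan leaves testers unmasked for a primary outcome, the 3-RM leg press, in which they select load and judge technique. Blinding the analysts does not protect it. The test can be run without knowledge of the diet arm. This is a design weakness, disclosed in the article, and not a contradiction.

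Its size is unknown. The rates of 8.5% and 19.5% rest on assumed biases of 3 and 6 percentage points, the stated SD of 30%, and 61 completers per arm from 152 in total. They show that a modest bias would matter, not that one exists. Masking without extra staff is likewise an assumption. The point merits a low-cost change to the remaining tests. It does not call for a redesign.

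**What to change.** For the week-24 strength tests not yet done:

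1. Do not give the arm to the existing staff who run the strength tests. Where the roster permits, assign this station to staff who do not handle diet diaries or monthly calls.
2. Ask participants not to mention their diet during testing.
3. Use one written script, identical in both arms, for load increments, technique criteria and encouragement.
4. Analyse DXA and pQCT scans under coded IDs.
5. Record every instance of unmasking.

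If the roster does not permit masking, keep the script and coded scans and report unmasked strength testing as a limitation.

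Cost: rostering, a short script and ID coding. The script and coding need no added assessor; masking may or may not, depending on who currently tests. N and planned power do not change. Downsides: some participants will reveal their arm, and bias from participants' own effort remains. Recruitment has begun, so the change reaches only later tests. Because recruitment and testing are split into two cohorts, a script introduced part-way could make tests before and after it less comparable, so its start date should be recorded and it should apply to both arms from the same day.
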